#### Economic analysis

Quantities of resources used (e.g. number of visits) will be combined with their unit costs and calculated from existing sources using standardised methods. Differences in the average cost per patient in each arm of the trial will be compared with differences in quitting rates. These are used to calculate incremental cost-effectiveness ratios (ICERs) for each intervention arm compared to the control arm.

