### Contingent reinforcement has been found to be effective in facilitating smoking cessation

A recent Cochrane review assessing smoking cessation interventions in pregnant women found that interventions that included an incentive component resulted in a significantly larger effect in point-prevalence abstinence during late-pregnancy, compared to other intervention strategies
[15]. Though PFI seems to be a potentially effective method in promoting smoking cessation in pregnant women, very few studies have assessed their effectiveness among pregnant smokers in an Australian antenatal care setting. Additionally, there have been no Australian studies which have assessed the effect of reward size on smoking cessation behaviour. One recent descriptive study found pregnant women had mixed and often unfavourable views regarding the acceptability and potential effectiveness of using PFIs to assist women to quit smoking
[21]. However, a significantly higher percentage of smokers reported favourable views on the use of PFI for smoking cessation, highlighting the ambiguity surrounding the acceptability and potential benefit of such a strategy
[21]. Consequently, it is important that research is conducted which aims to assess whether a PFI smoking cessation program is feasible in an Australian antenatal care setting.

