### Aims

The primary aim of this study is to test the feasibility of a personal financial incentive (PFI)-based intervention at encouraging smoking cessation in pregnant women attending an Australian public hospital for antenatal care. Specifically, the study will assess: (i) consent rates of women to participate in the trial; (ii) loss to follow-up rates of study participants; (iii) compliance with saliva cotinine and hair cotinine analyses for biochemical validation (iv) acceptability of using a touchscreen computer for self-reported smoking status and demographics; (v) acceptability of saliva cotinine and hair cotinine analyses for biochemical validation of smoking status; (vi) acceptability of incentives of varying magnitude ($20 vs. $40) to staff and study participants; and (vii) the perceived barriers and facilitators to using financial incentives in a public antenatal clinic among clinic staff. Additionally, secondary aims include: (i) to assess the potential effectiveness of the varying PFI amounts ($20 vs. $40) in reducing smoking among study participants; (ii) to assess the accuracy of self-report smoking status with saliva and hair cotinine analysis; and (iii) to undertake a cost-effectiveness analysis comparing the changes in costs of the intervention and changes in quit rates between each arm of the trial.

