### Intervention

Two intervention arms will be assessed: (1) a $AUD20 incremental personal financial incentive; and (2) a $AUD40 incremental personal financial incentive. Women from both intervention groups will have an opportunity to receive a PFI at eight study intervention sessions contingent upon smoking abstinence. The amount of the monetary reward will begin at the base amount (either $AUD20 of $AUD40) and will increase by the base amount (either $AUD20 of $AUD40) at each follow-up that participants are found to abstain from smoking. Smoking abstinence will be assessed through self-report and confirmed by saliva cotinine analysis. Participants in the $AUD20 intervention group, who quit smoking and maintain cessation for the entire eight intervention sessions, will be potentially eligible to receive a total of $AUD720. Participants in the $AUD40 group will be potentially eligible to receive a total of $AUD1440 if they maintain smoking abstinence for the 8 intervention sessions. If a participant fails to abstain at one intervention session or does not present for a scheduled visit they will not receive the incentive for that period. However, the reward amount these women will be eligible for during their next intervention session will be the amount they missed during their previous session. Their potential reward amount will remain at this amount until they have successfully stopped smoking.

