#### Economic outcomes measures

The feasibility of undertaking a cost-effectiveness analysis will also be undertaken. This will include the collection of data on the costs of the interventions that would include the amount of money received by each participant, and the costs of administering the payments in terms of staff time and other resources used. The intervention may also encourage patients to attend their antenatal visits, and potentially other health care visits associated with their pregnancy, more often than the control group, and so data will also be collected on patients’ utilisation of health services throughout the study. The feasibility of obtaining these data from Medicare, PBS, and hospital separations data, including obtaining patients’ consent, will be investigated and compared to gathering this data directly from patients using a standard questionnaire administered at each visit. The costs incurred by patients are also likely to be affected by the intervention. This will include savings in purchasing cigarettes, and differences in out of pocket, travel and time costs of attending if the intervention influences health care utilisation. These data will be collected from a short patient survey administered at each visit. Out of pocket costs for GP visits and prescribed medication can also be collected from MBS and PBS records. The effectiveness data on quitting will be collected as mentioned above, and combined with the data on costs. Incremental cost-effectiveness ratios (ICERs) will be calculated
[41].

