### Primary outcomes

Proportions and frequencies will be calculated to assess the following outcomes: (i) participant consent rates; (ii) loss to follow-up rates; and (iii) participant compliance with saliva and hair cotinine analysis. Proportions and frequencies will also be calculated for all closed-ended questions included in the study participant and clinic staff interviews to allow investigation of: (iv) participant acceptability of touchscreen computers for self-reported smoking rates and demographics; and (v) acceptability of incentives to staff and study participants. Differences between experimental groups in the proportion of each of these five primary outcomes and the secondary outcome (proportion quit smoking) will be assessed through Fisher’s exact test. Differences between participant subgroups and these outcomes will also be assessed using Fisher’s exact test. Although p-values from the above will be reported, the focus will be on providing 95% confidence intervals around point estimates for comparisons of all three treatment arms.

Qualitative analysis will be performed on open-ended questions included in participant and staff interviews investigating the following primary outcomes: (vi) acceptability of saliva and hair cotinine analyses for biochemical validation of smoking status; and (vii) perceived barriers and facilitators to using financial incentives. All interviews will be transcribed verbatim and a thematic analysis will be performed independently by two of the research team members.

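### The planned ICERs compare each incentive arm with control only, which is narrower than the economic aim and omits the $40 v $20 contrast that the reward-size question needs

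*Protocol article*

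**What the plan says.** Secondary aim (iii), in the Aims section of the protocol article, is a cost-effectiveness analysis "comparing the changes in costs of the intervention and changes in quit rates between each arm of the trial". Secondary aim (i) is "to assess the potential effectiveness of the varying PFI amounts ($20 vs. $40) in reducing smoking among study participants". The Background supports testing two reward sizes by noting that "there have been no Australian studies which have assessed the effect of reward size on smoking cessation behaviour".

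Economic outcomes measures introduces the economic work with "The feasibility of undertaking a cost-effectiveness analysis will also be undertaken" and ends with "Incremental cost-effectiveness ratios (ICERs) will be calculated", naming no comparator. The Economic analysis section first sets differences in mean cost per patient by arm beside differences in quit rates. It then fixes the ratios: these will be used to "calculate incremental cost-effectiveness ratios (ICERs) for each intervention arm compared to the control arm".

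For the feasibility outcomes and quit rates, the Primary outcomes section of the analysis covers every pair: "the focus will be on providing 95% confidence intervals around point estimates for comparisons of all three treatment arms". Nothing equivalent is said for the ICERs.

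**The concern.** Three arms give three pairwise contrasts, and the ICER rule names two of them. The one left out, $40 v $20, addresses the question that separates this design from a simple incentive v no-incentive trial.

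The three arms are mutually exclusive options. Standard incremental analysis compares each option with the next less costly option that is not dominated. If $40 is compared only with control, whatever the first $20 achieves is credited to the $40 arm as well. The resulting ratio can look the same whether the step from $20 to $40 buys many extra quitters, few or none. A reader choosing a reward size for a later trial could be misled by the two ratios that the plan names.

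**Working it through.** **Inputs from the protocol article**
- Maximum payment per woman (Intervention): $720 in the $20 arm and $1,440 in the $40 arm.
- Difference used in Sample size: 24 percentage points, with 30 women per group.

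**Inputs assumed, because the article gives no quit rates by arm and no unit costs**
- Control quit rate 6%, and so 30% in the $40 arm (6 + 24). At a control rate of 6%, the stated 68% power is roughly reproduced (68.6%, two-sided normal approximation).
- Only incentive payments count as cost. Every quitter earns the full schedule, non-quitters earn nothing, and control costs $0.
- The $20 arm's quit rate is varied from 8% to 30%.

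**Step 1: reproduce the stated payments.** The reward rises by the base amount at each of 8 sessions, so the total is base × (1 + 2 + … + 8) = base × 36. This gives 20 × 36 = $720 and 40 × 36 = $1,440. Both match.

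**Step 2: the averaging identity.** Write C for mean cost and E for quit rate, with ICER(a v b) = (Ca − Cb)/(Ea − Eb). Then

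ICER(40 v control) = w × ICER(20 v control) + (1 − w) × ICER(40 v 20), where w = (E20 − E0)/(E40 − E0).

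This is algebra and does not depend on the assumed figures.

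**Step 3: the illustration.** C40 = 0.30 × 1,440 = $432, so ICER(40 v control) = 432/0.24 = $1,800 in every row. C20 = 720 × E20.

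| $20 arm quit rate | C20 | $20 v control | $40 v control | $40 v $20 |
|---|---|---|---|---|
| 8% | $57.60 | 57.6/0.02 = $2,880 | $1,800 | 374.4/0.22 = $1,702 |
| 10% | $72.00 | 72/0.04 = $1,800 | $1,800 | 360/0.20 = $1,800 |
| 15% | $108.00 | 108/0.09 = $1,200 | $1,800 | 324/0.15 = $2,160 |
| 18% | $129.60 | 129.6/0.12 = $1,080 | $1,800 | 302.4/0.12 = $2,520 |
| 24% | $172.80 | 172.8/0.18 = $960 | $1,800 | 259.2/0.06 = $4,320 |
| 27% | $194.40 | 194.4/0.21 = $926 | $1,800 | 237.6/0.03 = $7,920 |
| 30% | $216.00 | 216/0.24 = $900 | $1,800 | 216/0: undefined, $40 dominated |

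Check of the identity at 24%: w = 0.18/0.24 = 0.75, and 0.75 × 960 + 0.25 × 4,320 = 720 + 1,080 = $1,800.

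**Step 4: read the two ends.** At 30%, the $40 arm costs twice as much as the $20 arm for no extra quitters, yet its planned ratio is still $1,800. At 8%, the $20 arm is extendedly dominated: its own ratio ($2,880) exceeds that of the step to $40 ($1,702). A sequential analysis would drop it and report $40 against control.

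**Step 5: precision.** Take 24% v 30% with 30 women per arm and simple binomial variances. SE = √(0.24 × 0.76/30 + 0.30 × 0.70/30) = √0.01308 = 0.114. The 6-point difference then has a 95% interval of 6 ± 1.96 × 11.4 points, about −16 to +28. A ratio with that denominator is barely informative.

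**The case against.** The strongest reply is that little is lost. The same section compares mean costs with quit rates across the arms. Once those differences are shown, $40 v $20 follows by subtraction and a dominated arm is visible. The economic work is partly a feasibility exercise within a proof-of-concept trial, and Step 5 shows how weak a $40 v $20 ratio would be. Aim (iii) does not name that ratio; the $20 v $40 wording belongs to the effectiveness aim, which the quit-rate analysis covers.

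Much of this stands, and it limits the point. Three stronger readings are tempting and should not be drawn:
- **That $40 v $20 cannot be estimated from this trial.** It can, from the same arm-level costs and quit rates. The gap is in which ratios are planned, not in the data.
- **That the $40 v control ratio must flatter the $40 arm.** The direction depends on unknown results. With the $20 arm at 10% the ratios agree, and at 8% the step from $20 to $40 is better value than $40 v control. It is also an assumption that $40 costs more overall, because the article counts service use and patient costs as well as payments.
- **That the plan is deficient for not describing how ICER uncertainty will be handled.** An article may leave that to the full protocol or analysis plan.

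What the reply does not remove is the mismatch. The article states the comparator explicitly, so this is not a detail left to another document, and the comparator is narrower than the article's own aim. The two control-based ratios alone do not in general determine the third; the underlying differences are needed, and the plan does not say that those for $40 v $20 will be reported.

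**Conclusion.** The point holds in a limited form. The ICER rule covers two of the three contrasts, whereas aim (iii) speaks of every arm and the reward-size question needs the third. The averaging identity is exact, so the $40 v control ratio alone cannot show whether $40 adds value over $20.

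On the assumptions listed, a constant planned figure of $1,800 goes with a $40 v $20 figure anywhere from about $1,700 to $7,920, or with dominance. Those dollar amounts only illustrate the range: they rest on assumed quit rates, payment costs only and full payment to every quitter. The practical consequence is modest, given the exploratory status of the economic work and 30 women per arm. The correction is still worthwhile because it brings the analysis into line with the aim at almost no cost.

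**What to change.** Amend the Economic analysis section to say that:
- the three arms will be ordered by observed mean cost;
- any dominated or extendedly dominated arm will be identified;
- each remaining arm's ICER will be reported against the next less costly non-dominated arm;
- the $40 v $20 differences in cost and quit rate will be shown in all cases, including when no meaningful ratio exists.

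The ratios against control can stay as supplementary results. The $40 v $20 result should be labelled exploratory.

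The cost is a few sentences of analysis wording and slightly more analysis of the same data. No extra data collection or recruitment is needed. The one downside is that a very imprecise ratio will be reported, which the label and the accompanying differences should make plain.

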### Ethics and safety approval

The study will be conducted in accordance with the Helsinki Declaration and has received ethical approval from both the Hunter New England Human Research Ethics Committee (Ref No: 11/09/21/4.05) and the University of Newcastle Human Research Ethics Committee (Ref No: H-2012-0047). Safety approval was also obtained from the University of Newcastle Health and Safety Review Committee (Ref: 26/2012).

## Discussion

The harmful effects of smoking during pregnancy are well known. Identifying strategies that are effective in reducing the number of women smoking during pregnancy and that are easily adopted into standard antenatal practice is of utmost importance. Despite numerous intervention studies attempting to address this issue very few have been successfully adopted into standard care. Given the past success of Personal-Financial Incentives in changing people’s health behaviours and being incorporating into routine care on a large scale, a similar strategy to assist women in quitting smoking seems to be a reasonable avenue for investigation. If the use of PFI as a strategy to reduce smoking during pregnancy is viable and acceptable to women and clinic staff, as well as illustrating promise of effectiveness, such a strategy has the potential to fill the current void in effective smoking cessation programs for pregnant women.

## Abbreviations

PFI: Personal Financial Incentive; RA: Research Assistant; RCT: Randomised control trial.
